### Data management

In order to monitor participant adherence to the weekly training sessions, a training sheet will be implemented that will i) show whether intervention group participants took part in the planned training sessions and ii) be used to document training progression. Participants will be contacted by email or phone if they fail to take part in two consecutive training sessions.

Additionally, as a safeguard for any potential data loss, all study data will be stored in a password-protected computer device that is not connected to the internet. Additionally, training documentation data of each participant will be entered in the computer device on a weekly basis to provide fast and easy access to training adherence and training progression.

### Data analysis

Statistical analyses will be performed by a statistician blinded to treatment groups. Level of significance is set at *p* ≤ 0.05. All values will be presented in means ± standard deviation. Statistical analyses will be conducted using the actual SPSS Version® (IBM®, Armonk, NY, USA) and R.

The required sample size to evaluate the between-group effect of the intervention on the primary outcome (serum changes of MMP-2 from baseline (T_0_) to post (T_2_)) in an analysis of covariance model (ANCOVA) was estimated using G*Power 3.1.9.2 [55]. Serum concentration of MMP-2 at baseline (T_0_) will be used as covariate. Based on already published study results [20], a medium to large effect size (Cohens d = 0.6) was used for sample size calculation. Statistical significance will be set 5% with statistical power (1-β) of 0.8. The sample size was calculated according to the formula N = (1-r2)*n described by Borm et al. [56]. The correlation was conservatively set at r = 0.6 which results in a preliminary sample size of *N* = 58. The expected drop-out rate is 15%. Therefore, a total of 64 participants will be recruited.

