**Methods:**

In this two-armed randomized controlled trial 64 participants with relapsing-remitting MS (RRMS) (EDSS 0–4.0) will be allocated to either an intervention group or a passive wait list control group. The intervention group will perform 60 min of combined functional resistance and endurance exercises 3x per week over a period of 12 weeks in a community-based and publicly available setting. Changes in serum concentration of MMP-2 will be the primary outcome. Secondary outcomes are numbers of immune cell subsets, soluble (anti-) inflammatory factors, physical capacity, cognitive performance, physical activity behavior, gait performance, and patient-reported outcomes. All outcome measures will be assessed at baseline and after week 12 with an additional blood sampling before, during and immediately after a single training session in week 6.

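### Recruiting 64 does not cover the stated 15% drop-out: about 54 remain analysable instead of the required 58, so power is about 77%, not 80%, at the plan's own inputs

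*Protocol article*

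**What the plan says.** The sample size paragraph under Data analysis in the protocol article sets out a short chain. The primary comparison is the between-group difference in MMP-2 change from T0 to T2, analysed by ANCOVA with baseline MMP-2 as covariate. The effect assumption is "a medium to large effect size (Cohens d = 0.6) was used for sample size calculation". The error rates are given as "Statistical significance will be set 5% with statistical power (1-β) of 0.8". The ANCOVA reduction is described as "The sample size was calculated according to the formula N = (1-r2)*n", and the result as "The correlation was conservatively set at r = 0.6 which results in a preliminary sample size of *N* = 58".

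The last step is "The expected drop-out rate is 15%. Therefore, a total of 64 participants will be recruited". The same total of 64 appears in the Methods part of the abstract and under Participants and recruitment.

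**The concern.** The second sentence of the last step is worded as a consequence of the first: 64 is presented as what 58 becomes once 15% drop-out is allowed for. The allowance actually made is 64 − 58 = 6 participants, whereas 15% of 64 is 9.6. An increase from 58 to 64 is about 10%, not 15%, so the stated drop-out rate and the recruitment target do not match.

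This paragraph is the sample size justification for the primary outcome. If the 15% expectation is right, the trial reaches its analysis with fewer participants than its own calculation requires, and the 80% power that readers will attach to the MMP-2 result is not what the design provides under its own assumptions.

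**Working it through.** **Inputs.** From Data analysis: d = 0.6; 5% level; power 0.80; r = 0.6; required N = 58; drop-out 15%; recruited 64. From Randomization: 1:1 allocation. Sidedness is not stated. Two-sided testing is assumed because it reproduces 58; one-sided testing gives 36 per arm, and 72 × 0.64 = 46.1, which cannot lead to 58.

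**Step 1: reproduce the plan's 58.** For a two-sample t-test (noncentral t), power at d = 0.6 is 0.795 with 44 per arm and 0.804 with 45 per arm. So n = 2 × 45 = 90.

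Applying the stated formula: N = (1 − r²) × n = (1 − 0.36) × 90 = 0.64 × 90 = 57.6, rounded up to 58. This matches the plan.

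**Step 2: allow for 15% drop-out.**

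| Calculation | Result | To recruit |
|---|---|---|
| 58 / (1 − 0.15) | 68.2 | 69 (70 for equal arms) |
| 58 × 1.15 (shortcut, too small) | 66.7 | 67 |
| 57.6 / 0.85 (unrounded start) | 67.8 | 68 |
| 58 × 1.10 | 63.8 | 64 |

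Only an allowance of about 10% gives 64. The more lenient normal approximation (44 per arm; 88 × 0.64 = 56.3) contradicts the stated 58 and, even with the shortcut, gives 56.3 × 1.15 = 64.8, so 65.

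**Step 3: what 64 delivers.**

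- Largest loss that still leaves 58: (64 − 58)/64 = 6/64 = 9.4%.
- Analysable at 15% loss: 64 × 0.85 = 54.4, so about 54, four short of 58.

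**Step 4: power.** For the baseline-adjusted comparison the effect in residual SD units is 0.6/√0.64 = 0.75. With equal arms the noncentrality is 0.75 × √(N/4), with N − 3 degrees of freedom and a two-sided 5% test.

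| Analysed N | Noncentrality | Power |
|---|---|---|
| 54 | 2.76 | 77.1% |
| 58 | 2.86 | 80.1% |
| 64 (no loss) | 3.00 | 84.0% |

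With N − 4 degrees of freedom, to allow for the lean body mass covariate named under Primary analysis, power at 54 is still 77.1%.

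**Step 5: detectable effect.** With 54 analysed, 80% power needs a residual-scale effect of 0.777. Multiplying by √0.64 = 0.8 gives d = 0.62, against d = 0.60 with 58.

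**The case against.** The arithmetic is hard to dispute; the fair counter-arguments concern its weight.

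- **The loss is small.** Three percentage points of power, and a detectable effect of 0.62 instead of 0.60, lie well within the uncertainty of the planning inputs. With 54 analysed, power returns to 80% if r is about 0.636 rather than 0.60, and the plan describes its r as conservative. This stands as a statement about size: the treatment estimate is not biased, no analysis changes, and a null result would be read mainly from the estimate and its interval.
- **The lean body mass covariate may help.** The sample size formula credits only the baseline correlation. If lean body mass explained about 7% of the variance left after baseline adjustment, 54 would give 80% power. The document gives no figure for this, so it remains a possibility and cannot support the stated number.
- **Intention-to-treat.** Participants who stop training could still give a T2 sample, and the article does not define drop-out. But a drop-out allowance is made precisely because some participants are expected to have no outcome value. If all 64 were expected to contribute, no allowance would be needed. Intention-to-treat does not supply missing serum samples.
- **A fuller protocol or SAP may exist.** Nothing is alleged to be missing. All the inputs and the result are printed together and disagree.

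What stands is that the practical effect is modest and the power figures are conditional on d = 0.6 and r = 0.6. None of it makes 64 follow from 58 and 15%.

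**Conclusion.** The sentence is wrong as written. The required 58 is correct for the stated inputs, but 64 does not follow from 58 with 15% drop-out: it covers a loss of at most 9.4%, and the full allowance needs 69 (70 for equal arms). At the stated drop-out about 54 are analysable and power is about 77%, roughly three points below the stated 80%; the effect detectable with 80% power is d = 0.62.

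These figures assume a two-sided 5% test, d = 0.6, r = 0.6, equal arms, and that a drop-out means no T2 MMP-2 value. The mismatch between 58, 15% and 64 needs only the last of these. The size of the error is small, but it sits in the justification of the primary outcome's sample size and anyone can check it.

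**What to change.** Correct the statement; recruiting more is not required. Any one of these makes the paragraph consistent:

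1. Keep 64 and 80% power, and say that this tolerates a drop-out of about 9%.
2. Keep 64 and 15%, and say that about 54 participants will be analysable, with power of about 77% at d = 0.6 and r = 0.6 (80% at d = 0.62).
3. Keep 15% and 80% power, and raise the recruitment target to 69, or 70 for equal arms (70 × 0.85 = 59.5 analysable).

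If 15% is still the honest expectation, the second is the plain choice without further recruitment. The first should be used only if there is reason to expect losses of 9% or less. Adding that the test is two-sided would let a reader reproduce the 58 directly.

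The first two options cost one corrected sentence, and the second a slightly less favourable stated power. The third costs five or six more participants, and the total of 64 would then also have to be changed in the abstract and under Participants and recruitment.

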### Primary analysis

An intention-to-treat analysis will be conducted. To investigate the effect of the intervention (12-week exercise intervention of combined functional resistance and endurance exercise) compared to control on the primary outcome MMP-2, we will conduct a 2 (intervention group vs. control group) × 2 (T_0_ vs. T_2_) analysis of covariance (ANCOVA). This model will be adjusted for baseline values and lean body mass at T_0_. As measure of effect size partial Eta-squared and Cohen’s d values, respectively, will be calculated.

### Secondary analysis

An intention-to-treat analysis will be conducted. To investigate the effect of the intervention compared to control on secondary outcomes, a baseline-adjusted 2 (intervention group vs. control group) × 2 (T_0_ vs. T_2_) ANCOVA model will be applied. To determine if groups differ at T_1_ and/or at T_2_, simple effects analyses (Bonferroni corrected) will be performed.

As measure of effect size partial Eta-squared and Cohen’s d values, respectively, will be calculated. Bivariate correlation analyses (Pearson) will be conducted to determine potential associations between changes in biomarkers and physical performance outcomes, cognitive performance and/or patient-reported outcomes from T_0_ to T_2_ (delta T_2_-T_0_).

To investigate the effect of an acute training session on biological markers in intervention group participants, we will conduct a repeated measures ANOVA at T_1_ (baseline), T_1.1_ (during) and T_1.2_ (post) exercise session.

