## Methods/design

In this study, a two-armed single-blind randomized controlled trial design will be applied. Prior to (T_0_) and 48 h after the intervention period (T_2_), an assessment of cardiovascular fitness, muscular strength, cognitive performance, gait performance and patient-reported outcomes (depression and anxiety, fatigue, quality of life, sleep quality, physical activity behavior, social integration) will be conducted. Blood samples at rest will be taken at T_0_, midpoint (T_1_) and T_2_. To investigate acute changes of BBB markers, immune homeostasis, (anti-) inflammatory factors as well as TRP metabolites, there will be an additional assessment of blood samples before (T_1_), during (T_1.1_) and after (T_1.2_) a training session with the resting values at T_1_ being further used for midpoint follow-up. Blood samples from the control group at T_1_ will be assessed without further measurements at T_1.1_ and T_1.2_. To control for the participants’ daily activity level, the participants will be asked to adhere to a 7-day actigraphic measurement on three time-points (T_0_,T_1_,T_2_).

All assessments and blood-sampling will be conducted at the German Sport University Cologne, except for the blood samples at T_1_,T_1.1_,T_1.2_ in the intervention group. This blood sampling will be done by a physician at the fitness center.

Due to the nature of the trial, participants could not be blinded to group allocation. Assessors taking outcome measures post intervention will be blinded to group allocation. The training sessions will be supervised by MS experienced exercise scientists. The trainers will not be involved in the post assessment to keep blinding.

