**Fig. 2 Fig2:**
[figure not shown]
Spirit diagram depicting the schedule of enrolment, interventions and assessments. T_0_ = baseline assessment before stratified randomization; T_1_ = collection of blood samples immediately before a training session at midpoint (6 weeks after intervention onset). Biomarkers at T_1_ will be further used for midpoint follow-up. Blood samples from the control group will be assessed at the German Sport University Cologne without further measurements at T_1.1_ and T_1.2_; T_1.1_ = collection of blood samples after resistance exercises; T_1.2_ = collection of blood samples immediately after the training session; T_2_ = assessment of outcomes 48 h after the last exercise session; * primary outcome; ** stratification factors: i) Bioimpedance analysis using lean body mass; ii) Cardiovascular fitness using Watt_max_; iii) Muscular strength using h1RM_sum_

Blood samples will be taken by qualified technicians via vein puncture from the antecubital vein in supine position at T_0_ and T_2_ at the German Sport University Cologne. Blood samples will be centrifuged at 3000 g for 10 min at 4 °C, and the supernatant will be stored at − 40 °C until study completion. MMP-2 will be determined by enzyme-linked immune sorbent assay (ELISA) (R&D Systems, Inc., Minneapolis, MN, USA) according to the manufacturer’s instructions.

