### Patient-reported outcomes

To assess physical activity behavior, both subjective and objective measures will be applied three times (T_0_,T_1_,T_2_).

For subjective measurement, the Godin Leisure-Time Exercise Questionnaire (GLTEQ) and the activity questionnaire will be used, respectively. The GLTEQ asks for weekly frequencies of strenuous (9 points), moderate (5 points), and mild (3 points) activities with all points being multiplied by the number of weekly conductance. Reference score units are ≥24 (≙ active), 14 to 23 (≙ moderately active) and < 14 (≙ insufficiently active) [45].

The second activity questionnaire is asking for the activity of the patients during the last 1, 6 and 12 weeks using either i) boxes to provide exact time of physical activity (in hours) and exercise (in minutes) during the last week and ii) visual analogue scales ranging from “low activity” to “high activity” to assess physical activity in the last 1, 6 and 12 weeks.

For objective measurement, an actimetry sensor (ActiGraph GT9X Link) is applied to each participant for seven consecutive days in order to identify differences in rest and activity cycles. The sensor will be attached to the hip to better monitor the activity level. There will be several interesting outcome measures with moderate to vigorous physical activity (MVPA) being the main outcome measure.

Fatigue will be assessed with the two-dimensional Fatigue Scale for Motor and Cognitive functions (FSMC). The FSMC has defined cut-off scores to differentiate between mildly (≥43 sum score), moderately (≥53 sum score) and severely (≥63 sum score) fatigued patients using 20 items with ten items for each dimension [46]. The German version shows excellent test-retest reliability [47].

Depression and anxiety will be measured with the German version of the Center for Epidemiologic Studies Depression Scale (CES-D) [48, 49]. In a 20-item measure using a four-point Likert scale, the participants will be asked to rate how often they experienced symptoms associated with depression over the past one to 2 weeks.

Health-related quality of life will be evaluated with the Multiple Sclerosis International Quality of Life Questionnaire (MusiQol) by describing nine dimensions with 31 items [50]. The German version shows good test-retest reliability [51].

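### The secondary analysis promises group comparisons at T1 from a model whose only time levels are T0 and T2, so the midpoint contrast cannot be obtained as written

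*Protocol article*

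**What the plan says.** In the protocol article, Secondary analysis, the between-group model for secondary outcomes is fixed in one sentence: "a baseline-adjusted 2 (intervention group vs. control group) × 2 (T_0_ vs. T_2_) ANCOVA model will be applied". The next sentence promises the follow-up contrasts: "To determine if groups differ at T_1_ and/or at T_2_, simple effects analyses (Bonferroni corrected) will be performed".

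Elsewhere T1 is set up as a real between-group time point:

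- Methods/design, sampling times: "Blood samples at rest will be taken at T_0_, midpoint (T_1_) and T_2".
- Methods/design, controls: "Blood samples from the control group at T_1_ will be assessed without further measurements at T_1.1_ and T_1.2". The control arm therefore contributes a resting T1 value.
- Methods/design, purpose: "with the resting values at T_1_ being further used for midpoint follow-up". The legend of Fig. 2 agrees: "Biomarkers at T_1_ will be further used for midpoint follow-up".
- Patient-reported outcomes, on physical activity: "both subjective and objective measures will be applied three times (T_0_,T_1_,T_2".

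The Secondary outcomes section places the assessments of physical and cognitive performance, patient-reported outcomes, body composition and motion analysis at T0 and T2 only. Physical activity is the exception, through the section quoted last.

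**The concern.** A simple effect of group is taken at a level of the time factor. The stated factor has two levels, T0 and T2, and the promised contrast is at a third time point that the model does not contain.

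An analyst who follows the text must therefore supply a model that the plan does not name. At least three are plausible: a separate ANCOVA at T1, a repeated-measures ANOVA with T0, T1 and T2 as levels, or a baseline-adjusted model with T1 and T2 as outcomes. They need not give the same estimate or p-value. The number of comparisons in the Bonferroni correction also depends on which is chosen. Across a panel of about twenty blood measures, that is analytic freedom which the plan evidently meant to close.

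The sentence is also written for secondary outcomes in general, although most of the non-blood outcomes have no T1 value.

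**Working it through.** **1. What the stated model can deliver.** Its cells are group (2) × time (T0, T2). Simple effects of group exist at T0 and at T2. The model is also adjusted for baseline, so T0 is both an outcome level and the covariate; given the T0 value, no variation at T0 is left to compare. The one informative group contrast is at T2. Of the two promised contrasts (T1, T2), the model yields one.

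**2. Whether another analysis supplies T1.**

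- Primary analysis: MMP-2 only, time levels T0 and T2. No T1.
- Acute-session analysis: repeated-measures ANOVA over T1, T1.1 and T1.2, in the intervention group only. No between-group comparison.
- Correlation analyses: changes from T0 to T2. No T1.

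No specified model compares the arms at T1.

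**3. Which secondary outcomes have a T1 value** (Immune cell counts; Soluble factors; Patient-reported outcomes).

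- Soluble factors explicitly given all time points: MMP-9, TNFα, IFNγ, IL-6, IL-17 and IL-10 (6), plus TRP, KYN, KYNA, QUIN and NAD+ (5). 6 + 5 = 11.
- Cell subsets: 4, each as number and proportion. 4 × 2 = 8.
- Total blood measures: 11 + 8 = 19.
- Physical activity: two questionnaires and actigraphy at T0, T1 and T2.

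MMP-2 is not counted, because it is the primary outcome and its analysis promises no T1 contrast. NfL and the three pathway enzymes are not counted, because the article gives no time points specific to them.

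**4. Size of the side benefit from using T1 data.** The contradiction above depends on no figure. The following only asks how much precision at T2 the T1 values could add. It borrows the planning values of the primary outcome (Data analysis section): d = 0.6, r = 0.6, alpha 5%, N = 64, drop-out 15%.

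The plan's own figure first. A two-sided two-sample t-test at d = 0.6 with 80% power needs 44.6, so 45 per arm and 90 in total. 90 × (1 − 0.6²) = 57.6, rounded up to 58, as stated.

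Assumptions not in the article: r = 0.6 between every pair of visits, loss at random, and normal approximation. The SD is set to 1.

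- Completers at T2 per arm: 64 × 0.85 / 2 = 27.2.
- Residual variance given T0: 1 − 0.36 = 0.64. Residual T1–T2 covariance: 0.6 − 0.36 = 0.24. Residual correlation: 0.24 / 0.64 = 0.375, squared 0.1406.
- T2 completers only: SE = √(2 × 0.64 / 27.2) = 0.2169. Power = Φ(0.6/0.2169 − 1.96) = 79.0%.
- With T1, if m per arm are lost after T1: SE = √(2 × 0.64 × [0.8594/27.2 + 0.1406/(27.2 + m)]).
  - m = 1.6 (5% of 64 in total): SE 0.2161, power 79.3%.
  - m = 4.8 (all 15%): SE 0.2146, power 79.8%.

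The gain is 0.3 to 0.8 percentage points. Across r = 0.5 to 0.8, with all 15% lost after T1, the SE falls from 0.2348 to 0.2329 (0.8%) at r = 0.5 and from 0.1627 to 0.1603 (1.5%) at r = 0.8.

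**The case against.** The strongest reply is that this is one imprecise sentence. The contrast (group at T1) and the correction (Bonferroni) are both stated, and a T0-adjusted ANCOVA at T1 is a natural reading. Much of that stands: the authors clearly intend to compare the arms at T1, and a competent analyst could do so. What does not stand is that the plan says how. It fixes a model and then a contrast outside it, so the gap is a contradiction in the article and not a detail left to a fuller document.

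Could T1 be a slip for T0? That does not help. A group contrast at T0 is uninformative in a baseline-adjusted model, and T1 is used consistently elsewhere for the midpoint.

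Three stronger readings are tempting, and the article supports none of them.

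- *Participants lost after T1 are excluded, so the intention-to-treat label is false.* The article says "An intention-to-treat analysis will be conducted" and gives no missing-data rule. Needing a T2 value is the default for such an ANCOVA, but imputation would fit the text equally well, and an article commonly leaves this to the full protocol or analysis plan. The 15% drop-out (64 × 0.15 = 9.6) carries no timing, so the number who would have a T1 but no T2 value is unknown.
- *The midpoint data are discarded.* The stated model omits them, but the promised contrast and the midpoint follow-up wording show the opposite intention.
- *The primary analysis must change too.* Its text contains no T1 contrast, the trial was sized for that ANCOVA, and on the primary outcome's planning values the gain from adding T1 is under 1 point of power. Replacing it would be a preference, not a correction.

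**Conclusion.** The point holds in its narrow form. The T1 group contrast promised for secondary outcomes cannot be produced by the only between-group model specified for them, and nothing else in the article supplies it. It affects 19 explicitly timed secondary blood measures and physical activity. For most physical, cognitive and patient-reported outcomes the T1 wording has no data behind it at all. This conclusion rests on the text alone.

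It should be corrected before analysis, because the choice of model and Bonferroni family is otherwise open. It does not touch the primary result, and it does not show that anyone is excluded. The precision gain from T1 is small under the stated assumptions. If loss depended on measured T1 values, using them would also guard against bias, but the article gives nothing from which to size that.

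**What to change.** - **Secondary outcomes measured at T1 in both arms:** replace the T0/T2 model with one baseline-adjusted repeated-measures mixed model. Outcome visits are T1 and T2; terms are visit, T0 value × visit and group × visit, with unstructured covariance over the two visits. Include all randomised participants with any post-baseline value. Read the T1 and T2 group contrasts from it, Bonferroni-corrected over the two (0.05 / 2 = 0.025 each). T0 is then a covariate only.
- **Secondary outcomes measured only at T0 and T2:** use ANCOVA of the T2 value on the T0 value and group, and remove the T1 wording for them.
- **NfL and the enzymes:** state whether they are measured at T1, so that each falls clearly under one of the two rules.
- **Primary MMP-2 ANCOVA:** no change is needed on this point.

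The cost is a few lines of analysis wording and standard mixed-model code in the software already named. No new data, visits or participants are required.

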## Discussion

Disability in pwMS often continues to worsen despite immunotherapy, so alternative and/or adjunct treatments seem imperative for this patient cohort [1]. Besides the need of encouraging pwMS to engage more in moderate to vigorous exercise [6], existing (multimodal) therapeutic exercise regimens need to be continuously optimized in order to decrease the socioeconomic consequences of MS and to improve the quality of life of pwMS. In this study only persons with a relatively low disease severity (EDSS 0–4) will be included. Due to the fact that the disease-specific symptomatology is limited only to a few systems, the probability to include participants in an early disease state is increased. That in turn allows to take advantage of a proposed “window of opportunity” that may be a promising approach to effectively slow down disease progression [29].

Moreover, the approach of this study, i.e. community-based training with combined functional resistance and endurance exercises in a publicly available fitness center, may have profound impact on general feasibility of effective exercise treatments and optimization of existing exercise recommendations.

Improving the BBB integrity by reducing MMP-2 serum concentration as the primary outcome of this study and to establish immune homeostasis seem to be an integral component for decreasing both MS-specific symptomology and disease progression.

Another important objective of this study is to test assumptions of existing hypothetical biopsychosocial models in pwMS [9, 10] in the context of exercise neuroimmunology by correlating the assessed cognitive capacity and patient-reported outcomes like anxiety/depression and fatigue with immune-related biomarkers and cell populations. Moreover, the assessment of the acute effect will extend knowledge of acute exercise-induced effects on immune signaling, proportions on immune cell subsets and the kynurenine pathway in persons with RRMS.

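### The planned Pearson correlations of change scores carry no term for arm, so a training effect on both variables can appear as a biomarker–symptom association

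*Protocol article*

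**What the plan says.** The Secondary analysis section names the method: "Bivariate correlation analyses (Pearson) will be conducted to determine potential associations between changes in biomarkers and physical performance outcomes, cognitive performance" and/or patient-reported outcomes, using the difference between T2 and T0. It mentions no arm term, partial correlation, within-arm split or regression. Elsewhere in that section, the between-group models are explicitly baseline-adjusted and the acute-session analysis is explicitly limited to intervention participants. The correlation sentence has neither kind of qualifier.

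The correlations have a stated purpose. The Discussion says: "Another important objective of this study is to test assumptions of existing hypothetical biopsychosocial models in pwMS", and that this will be done "by correlating the assessed cognitive capacity and patient-reported outcomes like anxiety/depression and fatigue with immune-related biomarkers and cell populations". The last paragraph of the Background gives the same aim.

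The only effect size in the document is in Data analysis, for MMP-2: "a medium to large effect size (Cohens d = 0.6) was used for sample size calculation".

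**The concern.** The trial is built so that arm moves the variables being correlated. The sample size assumes an effect on MMP-2, and the programme trains strength and endurance directly. When two groups with different means on both axes are plotted together, the cloud tilts even if there is no tilt inside either group.

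A correlation arising in that way repeats what the group comparisons already show, namely that training changed both variables. It does not show that participants whose marker fell more also improved more in fatigue or cognition, which is the evidence a biopsychosocial model needs. At stake is the interpretation of an objective that the authors call important.

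**Working it through.** **The plan's own figure.** The document gives no figure for the correlations, so the check starts from its sample size.

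- Inputs from Data analysis: "Statistical significance will be set 5% with statistical power (1-β) of 0.8", d = 0.6, and "The correlation was conservatively set at r = 0.6" between baseline and follow-up.
- A two-sided two-sample t-test needs 45 per arm, 90 in total.
- 90 × (1 − 0.6²) = 90 × 0.64 = 57.6, so 58. This matches the stated preliminary N. The article does not state sidedness; a one-sided test would give 47.

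**Correlation induced by arm.** Take 1:1 allocation (Randomization section), zero correlation within each arm, and arm shifts d1 and d2 in units of the within-arm SD of change. Then

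r = (d1·d2/4) / √[(1 + d1²/4)(1 + d2²/4)]

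- 0.6 and 0.6: 0.09 / 1.09 = 0.083
- 0.6 and 1.0: 0.15 / √(1.09 × 1.25) = 0.129
- 1.0 and 1.0: 0.25 / 1.25 = 0.200
- 0.6 and 0: numerator zero, so r = 0

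The plan's 0.6 can also be converted to change-score units using its r = 0.6: 0.6 / √(2 × (1 − 0.6)) = 0.67. On both variables this gives 0.1125 / 1.1125 = 0.101.

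**How often p ≤ 0.05 follows.** Simulation with 40,000 trials per scenario, N = 58, normal data; the critical |r| is 0.26.

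| Shifts (SD) | Pooled r | Significant, no arm term | Significant, arm-adjusted |
|---|---|---|---|
| 0.6, 0 | 0.00 | 4.9% | 5.0% |
| 0.6, 0.6 | 0.08 | 9.3% | 5.1% |
| 0.67, 0.67 | 0.10 | 11.6% | 5.0% |
| 0.6, 1.0 | 0.13 | 16.1% | 4.8% |
| 1.0, 1.0 | 0.20 | 33.5% | 5.1% |

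The result depends little on the final sample: with 0.6 on both, N = 54 gives 9.0% and N = 64 gives 9.9%.

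Only 0.6 for MMP-2 comes from the document. Applying 0.6 to a second variable, and every 1.0 SD shift, is an assumption.

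**Number of possible pairs (context only).** The outcome sections list 4 cell subsets and 13 soluble markers, so 17. Three enzymes bring this to 20, and counting cell proportions separately to 24. On the other side are 3 physical, 3 cognitive and 6 questionnaire outcomes, so 12; with gait, actigraphy and subscales, perhaps 20. That gives 17 × 12 = 204 to 24 × 20 = 480 pairs.

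**The case against.** Four points can be made for the plan.

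- **Pooling is not stated.** If the correlations are run within each arm, the artefact disappears. This is correct, but an unrestricted sentence beside one that is expressly limited to the intervention group reads as both arms together. If within-arm analysis is meant, the text needs to say so.
- **The size is modest at the plan's effect.** A reader might infer that the correlations will be mostly artefact, or will reflect nothing but training. The documents do not support that. At 0.6 SD on both variables the rate goes from 5% to about 9%, and if training moves only one variable it does not rise at all. The high rates need assumed shifts of about 1 SD. Such a shift is easiest to imagine for fitness, whereas the biopsychosocial aim concerns cognition, fatigue and mood, for which no training effect is given. This objection stands and limits the claim.
- **The pooled correlation is a real quantity.** In the simulation it truly is 0.08 or 0.20, so rejecting zero is an error only if the target is the association within arms. That is so, but the Discussion's stated use requires the within-arm association.
- **Multiplicity.** A reader might also infer that the lack of a correction over hundreds of pairs is an error. The article ties Bonferroni to the group comparisons ("simple effects analyses (Bonferroni corrected) will be performed") and is silent on the correlations. A short list of pairs or a false-discovery rule can properly sit in an analysis plan that is not shown, and the article does not say that every pair will be tested. The count supports an exploratory label and no more.

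**Conclusion.** The concern holds for the missing arm term. The article fixes a method that, on its natural reading, mixes the between-arm training effect with the association that the authors want to study. The consequence ranges from none (one variable moved), through about 9% (0.6 SD on both), to about a third of tests nominally significant (1.0 SD on both).

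These figures assume pooled arms, equal allocation, 58 analysed participants, normal changes and no within-arm correlation. The defect affects a secondary objective that the authors themselves call important. It does not touch the MMP-2 comparison.

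**What to change.** In the Secondary analysis section, replace the bivariate Pearson correlation with an arm-adjusted association. This can be a partial correlation given arm, or a regression of outcome change on biomarker change with arm and both baseline values in the model. State that both arms contribute. Describe the results as exploratory, given roughly 200 to 480 possible pairs.

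The cost is a few lines of wording and one degree of freedom for arm (plus two if the baselines are included), with no new data or visits. Fewer pairs will probably reach nominal significance.

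Arm adjustment removes the shared training effect, but it does not turn the remaining association into evidence of mediation, and the report should say so.
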